# Feasibility assessment of the Eye Scan Ultrasound System for cataract characterization and optimal phacoemulsification energy estimation: protocol for a pilot, nonblinded and monocentre study

**DOI:** 10.1186/s40814-022-01173-2

**Published:** 2022-09-29

**Keywords:** Cataract, Ultrasound, Diagnosis, Phacoemulsification surgery

## Abstract

**Background:**

Cataracts are lens opacifications that are responsible for more than half of blindness cases worldwide, and the only treatment is surgical intervention. Phacoemulsification surgery, the most frequently performed cataract surgery in developed countries, has associated risks, some of which are related to excessive phacoemulsification energy levels and times. The protocol proposed in herein will be used to evaluate the feasibility of a new experimental medical device, the Eye Scan Ultrasound System (ESUS), for the automatic classification of cataract type and severity and quantitative estimation of the optimal phacoemulsification energy.

**Methods:**

The pilot study protocol will be used to evaluate the feasibility and safety of the ESUS in clinical practice. The study will be conducted in subjects with age-related cataracts and on healthy subjects as controls. The procedures include data acquisition with the experimental ESUS, classification based on the Lens Opacity Classification System III (LOCS III, comparator) using a slit lamp, contrast sensitivity test, optical coherence tomography, specular microscopy and surgical parameters.

ESUS works in A-scan pulse-echo mode, with a central frequency of 20 MHz. From the collected signals, acoustic parameters will be extracted and used for automatic cataract characterization and optimal phacoemulsification energy estimation.

The study includes two phases. The data collected in the first phase (40 patients, 2 eyes per patient) will be used to train the ESUS algorithms, while the data collected in the second phase (10 patients, 2 eyes per patient) will be used to assess the classification performance. System safety will be monitored during the study.

**Discussion:**

The present pilot study protocol will evaluate the feasibility and safety of the ESUS for use in clinical practice, and the results will support a larger clinical study for the efficacy assessment of the ESUS as a diagnostic tool. Ultimately, the ESUS is expected to represent a valuable tool for surgical planning by reducing complications associated with excessive levels of phacoemulsification energy and surgical times, which will have a positive impact on healthcare systems and society. The study is not yet recruiting.

**Trial registration:**

ClinicalTrials.gov identifier NCT04461912, registered on July 8, 2020.

## Introduction

### Background

Cataracts account for over half of blindness cases worldwide, with the only established treatment being the surgical removal of the cataractous lens and replacement with an intraocular lens (IOL) [1, 2]. Several scientific contributions were crucial to the evolution of cataract surgery. The first key finding was identified in the mid-twentieth century for Second World War fighter pilots, in which intraocular fragments of shattered acrylic from canopies were well tolerated. This fact led to the development of the first IOL using this material [3]. In approximately 1960, A-scan ultrasonic systems emerged for measuring the axial eye length [4], which allowed to determine the refractive power of the IOLs, thereby reducing the previously significant postoperative refractive errors [3, 4]. In 1967, high-precision ultrasonic equipment working at 10 MHz was further developed, which solved some remaining limitations of the previous systems, such as the deformation produced by the probe over the cornea, inability to perform alignments within the visual axis and large beam diameters [5]. Moreover, in the same year, the first phacoemulsification surgery was performed using ultrasonic waves for fragmentation of the cataractous lens [6]. This technique introduced a more controlled, faster and safer method of extracapsular cataract extraction, which provided significant advantages for cataract treatment.

Cataract surgery has evolved in recent years, thus making the method safer and more efficient. However, risks are still associated with this procedure. Among them, posterior lens capsular rupture and corneal endothelial cell loss related to excessive levels of phacoemulsification energy represent approximately 5 to 10% of postoperative complications [7, 8]. Posterior capsular rupture has diverse associated risks such as vitreous loss and dropped nucleus, increasing the risk of cystoid macular oedema or retinal detachment. In turn, corneal oedema and opacification may result from corneal endothelial cell loss. These complications may limit or prevent visual recovery [7].

Acoustic parameters extracted from ultrasonic waves propagating in cataractous lenses have been widely studied to characterize their structural and biomechanical properties. Several studies have characterized the presence and severity of cataracts using this approach [4, 8–12]. Moreover, studies have used ultrasound for cataract hardness estimation [8, 13–20] since the efficient energy that must be applied to phacoemulsification surgeries is directly related to cataract hardness [17]. Most of these studies were conducted in porcine lenses due to the similarities in their acoustic parameters with human lenses [21].

Preclinical studies were conducted by the research team with two models of cataracts: ex vivo in porcine lenses [8, 20] and in vivo in rat lenses [12]. These studies evaluated several automatic classification methods for cataract hardness and severity based on features extracted from the ultrasonic signals. The results showed a precision, sensitivity and specificity of 99.7% for cataract severity classification, as well as a statistically significant difference in lens hardness for the different cataract severities [12].

The present pilot study protocol aims to evaluate the Eye Scan Ultrasound System (ESUS), which was developed in the preclinical studies [22] and adapted for clinical applications [23] in human lenses in vivo. Because it is a first in human study, and to reduce risks and optimize human and financial resources, a pilot protocol was designed for feasibility assessment of the ESUS in clinical practice. It aims to assess the feasibility of detecting and characterizing human cataracts by ultrasound and the suitability and safety of the technique for use in clinical practice. Related to cataract characterization, the study protocol was designed to evaluate the performance of the experimental medical device ESUS for the automatic classification of cataract type and severity based on the Lens Opacity Classification System III (LOCS III, [24]) and to estimate the optimal phacoemulsification energy (OPE).

The study protocol is organized in two phases. In the first phase, the collected data will be used for training the automatic detection and classification algorithm for human cataracts. In the second phase, the collected data will be used for a preliminary assessment of the algorithm performance. Cataracts classified according to the LOCS III for type and severity [24] will be used as comparators. Safety will be evaluated throughout the study.

The experimental medical device may represent an important advance in cataract treatment based on two main contributions. First, cataracts should be detected at incipient stages, even before the onset of symptoms, in patients at high risk of developing cataracts. At incipient stages, visual acuity is preserved, which may favour the outcomes of emerging pharmacological therapies [1, 25]. On the other hand, with ESUS, it is expected to achieve quantitative and automatic estimation of OPE. It may represent a valuable tool in surgical planning by reducing complications associated with excessive levels of phacoemulsification energy and excessive surgical times [7]. These advances are relevant not only for patients but also for public health systems because they may reduce waiting lists and associated costs.

Further clinical studies will be needed to enlarge the database to improve the performance of cataract classification and better evaluate the technique’s efficacy and to include other causes of cataracts since only age-related cataracts are considered in the present protocol.

The manuscript follows the SPIRIT [26] and CONSORT [27] reporting guidelines and checklists and the editorials [28, 29].

### Objectives

#### Primary objective

Evaluate the feasibility of the ESUS (experimental medical device) for cataract characterization in humans.

#### Secondary objectives

i.Automatically detect and classify cataracts according to their type and severity.ii.Detect cataract in the incipient stage.iii.Estimate the OPE.iv.Assess the automatic classification performance.v.Evaluate the safety of the ESUS.

## Methods

### Trial design

Pilot, nonblinded and monocentre study.

### Participants

#### Study setting

The participants will be recruited from patients who have a medical consultation scheduled at the clinical centre (Coimbra Surgical Centre, Portugal).

Two groups are considered in this study. For the cataract group, the patients will be invited to participate after being diagnosed with cataracts and referred to phacoemulsification surgery by the physician. For the control group, the patients will be invited to participate after the presence of cataracts is excluded. For both groups, the inclusion/exclusion criteria must be verified.

#### Inclusion and exclusion criteria

##### Inclusion criteria

i.Between 50 and 70 years oldii.Either genderiii.Cataract group○ Patients with age-related cataract○ Indication for phacoemulsification surgeryiv.Control group○ Patients without cataractxxii.Signed consent

##### Exclusion criteria

i.The presence of any other ophthalmological condition or systemic disease that could affect the results.

#### Recruitment procedure and informed consent

Medical investigators of the research team will recruit the participants. He/she must inform the patients about the study objectives, the procedures involved, the visit schedule, the benefits and risks of their participation, the privacy policies and the freedom to participate or withdraw. The investigator must provide enough time for consent form reading and clarify all doubts. If the patient agrees to participate, he/she (or their legal representative) and the medical investigator must sign the consent form. One copy of the consent form will be given to the participant, and the original document will be kept at the clinical centre.

#### Participation time and anticipated withdrawal

The maximum participation time for each subject is 3 months. Participant inclusion will be confirmed on the same day that cataracts are diagnosed or excluded. Participants in the control group will complete the procedures on the same day, and a remote follow-up will be conducted 1 week later. Participants in the cataract group will complete the study on the day of the second postoperative follow-up (1 month after surgery). If the second eye receives an indication for phacoemulsification surgery, data for this second eye will also be collected.

An anticipated withdrawal of the participants is considered in the following situations: the occurrence of any unanticipated adverse effects, anticipation of a risk situation, any physical condition that makes it impossible to conduct the procedures involved in the study, or the voluntary withdrawal of the participant. In all these cases, the causes for participant withdrawal should be registered in the individual case report form (CRF), and the participants will be encouraged to perform a final follow-up. Codified data collected before the participant withdrew can be used for the purpose of the study.

#### Sample size and allocation

In the first phase of the clinical study, forty participants will be included, and the two eyes will be studied. The participants will be equally distributed into four groups (based on slit lamp/LOCS III classification): participants with incipient, moderate and severe cataracts and participants without cataracts will be included as the control group. The second phase will include at least ten participants, and the two eyes will be studied. Safety will be evaluated for all the recruited participants along the first and second phases.

Since this is a protocol for a pilot study, no sample size estimate was performed. The number of eyes expected to be analysed along the study (i.e. 20 per arm) was considered adequate for this study [30]. The statistical power will be determined at the end of the study for statistically significant results.

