#### Demographic and medical record

This information will be obtained from the patient record at the clinical centre with the purpose of confirming the inclusion/exclusion criteria and identifying biases. The data to be recorded are birth date, sex, occupation history, smoking and drinking habits and history of any ophthalmic or systemic diseases and associated treatments.

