## Discussion

Preclinical studies showed that the experimental device presented positive performance for cataract classification and did not identify potential risks when used within the safety range by trained professionals. The present protocol refers to the first human pilot study of the experimental medical device ESUS. This study aims to evaluate the feasibility and safety of ESUS for quantitative and automatic cataract characterization and OPE estimation in human lenses. It is expected that the obtained results will be used in a larger clinical study to increase the dataset, to improve the performance of the algorithms for automatic classification and to train the algorithms for other causes of cataracts (in addition to age-related cataracts).

Several measures have been taken to minimize bias in the clinical study. The acquisition software was optimized to identify the correct probe positioning, thereby minimizing errors due to misalignment. The cataract group will be limited to age-related cataracts to reduce divergences in clinical conditions that could influence the results. A number of demographic and clinical information from participants will also be analysed for the identification of any additional source of bias.

The clinical study protocol presented here is a key piece of long-term translational research. The quantitative characterization of cataracts and estimation of OPE could significantly reduce postoperative complications and surgical times related to phacoemulsification surgeries, thus providing important social and economic benefits.

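### Phase 1 groups are filled by presence and severity of an age-related disease with no balance on age, so the classifier could partly learn age, and phase 2 would not reveal it

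*Protocol article*

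**What the plan says.** All references are to the protocol article.

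- **Who enters.** One age criterion, 50 to 70 years, covers both groups (Inclusion criteria). Cases are "Patients with age-related cataract" with an indication for surgery. The only control-specific criterion is absence of cataract. Study setting adds how controls are found: "For the control group, the patients will be invited to participate after the presence of cataracts is excluded".
- **How groups are filled.** In phase 1, "forty participants will be included, and the two eyes will be studied", and "The participants will be equally distributed into four groups (based on slit lamp/LOCS III classification": control, incipient, moderate and severe. For the test phase, "The second phase will include at least ten participants, and the two eyes will be studied". No age balance is stated for either phase.
- **Bias measures.** The Discussion lists software that checks probe position, then restriction by cause ("The cataract group will be limited to age-related cataracts to reduce divergences in clinical conditions that could influence the results"), then an analysis of demographic and clinical data to look for other sources of bias. Birth date is among the items recorded, "with the purpose of confirming the inclusion/exclusion criteria and identifying biases" (Demographic and medical record).
- **Success criteria.** Feasibility assessment requires the device to pick up at least 90% of the cataracts seen at the slit lamp, and a classification sensitivity above 90%. Neither target has a specificity term.

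**The concern.** When groups are defined by presence and severity of an age-related condition, sorting by group may also sort by age. Restricting cases to one cause makes the cataracts more alike, but it does not make controls and cases alike in age. The shared 50 to 70 window limits the possible gap, yet still spans 20 years.

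The classifier sees acoustic features only. If those features carry information about age in lenses without opacity, an algorithm trained on age-imbalanced groups can use it to separate cases from controls. Phase 2 uses new participants but recruits them in the same way, so the same imbalance could recur and the shortcut would look like performance.

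This bears on the intended use. The Introduction hopes to detect cataract at incipient stages, before symptoms, in patients at high risk. There the device has to tell early opacity from age. The results are also meant to support a larger study.

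**Working it through.** **Inputs from the article.** 40 phase 1 participants, four equal groups, two eyes each; ages 50 to 70; at least 10 phase 2 participants; 90% detection target.

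**The plan's own figure.** 40 / 4 = 10 participants per group, and 10 × 2 = 20 eyes, which reproduces the 20 per arm in "The number of eyes expected to be analysed along the study (i.e. 20 per arm) was considered adequate for this study". Cases to controls are 30 to 10. Both eyes of a participant have the same age, so for age balance the control group has 10 independent values, not 20.

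**Inputs not in the article.** No ages by group are given. I assume a within-group SD of 4 to 5 years and show a range of mean gaps (cases minus controls).

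**How well age alone separates the groups.** With normal ages and equal SDs, AUC = Φ(gap / (SD × √2)). With the cut-off set at 90% sensitivity, specificity = Φ(gap / SD − 1.28).

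| Gap (years) | AUC, SD 5 | AUC, SD 4 | Specificity, SD 5 | Specificity, SD 4 |
|---|---|---|---|---|
| 0 | 0.50 | 0.50 | 10% | 10% |
| 2 | 0.61 | 0.64 | 19% | 22% |
| 5 | 0.76 | 0.81 | 39% | 49% |
| 8 | 0.87 | 0.92 | 62% | 76% |

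For example, a gap of 5 with SD 5 gives Φ(1 / 1.414) = Φ(0.707) = 0.76. These figures treat age as known exactly. Acoustic features that track age only loosely would do worse, so they are upper bounds on an age-driven signal.

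**Imbalance by chance.** If ages were uniform on 50 to 70 in both groups, SD = 20 / √12 = 5.8 years. The standard error of the difference in mean age is 5.8 × √(1/10 + 1/30) = 2.1 years. A gap of about 2 years is therefore unremarkable even with no systematic tendency.

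**Is age what lets the target be met?** In a simulation of 4,000 runs per setting, a linear discriminant used age only. It was trained on 30 cases and 10 controls, with ages truncated to 50–70 (SD 5 before truncation), and tested on an assumed 8 cases and 2 controls. Success was observed sensitivity of at least 90%, which with 8 cases means all 8, since 7 / 8 = 87.5%.

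| Mean gap (years) | Mean sensitivity, 3:1 prior | Mean specificity, 3:1 prior | Target met, 3:1 prior | Target met, equal priors |
|---|---|---|---|---|
| 0 | 99% | 1% | 95% | 1% |
| 3.1 | 95% | 14% | 73% | 4% |
| 5.2 | 92% | 41% | 55% | 10% |
| 7.1 | 92% | 62% | 53% | 21% |
| 8.9 | 94% | 77% | 60% | 36% |

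Under the design's 3:1 mix, the target is met most often when age carries no information, because the rule then calls almost everyone a case. Calling every eye cataract gives 100% sensitivity, 0% specificity and 30 / 40 = 75% training accuracy. With equal priors, a wider age gap does raise the pass rate, but only to 36%.

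**The case against.** The strongest reply is that the essential link is missing from the documents. The Introduction speaks of acoustic parameters in cataractous lenses. Nothing says that the acoustics of a clear lens change with age, and age is not a listed classifier input. This stands, and it keeps the point conditional.

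Three stronger readings are tempting and are not supported.

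- A reader might infer that controls will cluster near 50 and severe cases near 70, with hardly any overlap. The article gives no ages by group, and every case, including the incipient ones, needs a surgical indication. Even an 8-year gap with SD 4 leaves two normal curves overlapping by 2Φ(−1) = 32%.
- A reader might infer that age imbalance is what makes the 90% detection target easy to pass. The simulation shows that the sensitivity-only criterion and the 3:1 mix are the main reason.
- A reader might infer that age was overlooked altogether. The shared age window restricts it, and birth date is recorded partly to look for bias.

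It can also be said that a statistical analysis plan may set out how demographics are used, and that a first-in-human pilot need not be fully controlled. Both are fair as far as they go. But group composition is settled at recruitment. If ages overlap poorly, later adjustment with 10 controls has little to work with. The article states its allocation rule and its main bias measures, and none of them balances age.

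**Conclusion.** The point holds as a possibility, not a prediction. Groups are filled by presence and severity of an age-related disease with no age balance, so age may differ between controls and cases. If clear-lens acoustics vary with age, part of any apparent detection or severity performance could be age, and phase 2 would not expose it. The demographic review can identify an imbalance but not remove it.

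The size cannot be established from the documents. The AUCs in the first table rest on an assumed SD and assumed gaps, and they range from weak separation at 2 years to strong separation at 8.

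Balancing age takes the age information away (AUC 0.50 at no gap) but leaves the detection criterion as easy to meet as before. The two matters need separate remedies. This is an inexpensive improvement to make before recruitment, not an error that invalidates the pilot.

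**What to change.** 1. In Sample size and allocation, frequency-match controls to cataract participants by age band, for example 50–54, 55–59, 60–64 and 65–70, in both phases.
2. Report ESUS detection and severity classification beside a benchmark that uses age alone, taken from the recorded birth date. The severity benchmark matters because matching controls does not balance age among the incipient, moderate and severe groups.
3. Report specificity in controls, or AUC, with the detection sensitivity. In phase 2 this will be descriptive, given the numbers.

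The cost is somewhat slower recruitment of controls, since about 10 cataract-free participants in the required age bands must be found in phase 1 plus those for phase 2, and one extra analysis. No new procedures or additional participants are needed.

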#### Cataract type and severity estimation

The automatic classification system will classify the cataract type (nuclear, cortical, or posterior subcapsular) and evaluate the severity.

From the acquired ultrasonic signals, several acoustic parameters in the time and frequency domains will be extracted. Then, more representative parameters will be selected through a principal component analysis and used for automatic classifier training (e.g. support vector machine, Bayes network and random forest). The performance of the different classifiers will be compared. The classification obtained by a trained specialist using the LOCS III will be used as a reference.

In the second study phase, a preliminary evaluation of the automatic classification performance will be conducted using a new dataset. It will be considered suitable if it reaches sensitivity levels higher than 90%, with a maximum significance level of 5%.

All the participants/eyes performing the ESUS study will be included in the analysis.

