#### OPE estimation

To develop an OPE estimator, the acoustic parameters extracted from the ultrasonic signals in the first phase will be correlated with the maximum energy used in the phacoemulsification surgery for each participant eye. Only surgeries without surgical or postoperative complications will be considered. A confidence interval of 95% followed by multiple comparison correction will be used to assess the significance of the correlations.

In the second phase, the acoustic parameters extracted from the ultrasonic signals will be used to predict the safety and risk intervals of phacoemulsification energy based on the correlation curves. To evaluate the prediction accuracy, surgeons should initiate surgeries at minimum energy levels and increase them gradually until they reach an efficient energy level. Then, the maximum energy level applied during surgery and the occurrence of surgical and/or postoperative complications will be compared with the safe and risk energy intervals predicted with the correlation curves. The system efficacy will be considered suitable if the prediction accuracy is higher than 90%.

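### Groups are formed by participant but the size is justified by eyes (20 per arm is both eyes of 10 people), and the per-eye energy correlations make no stated allowance for pairing

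*Protocol article*

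**What the plan says.** Under Sample size and allocation, the unit recruited and grouped in phase 1 is the participant: "forty participants will be included, and the two eyes will be studied", and "The participants will be equally distributed into four groups (based on slit lamp/LOCS III classification", with three cataract severities and a control group. For phase 2, "The second phase will include at least ten participants, and the two eyes will be studied". There is no power calculation ("Since this is a protocol for a pilot study, no sample size estimate was performed"). What stands in its place is a count of eyes, supported by a cited reference: "The number of eyes expected to be analysed along the study (i.e. 20 per arm) was considered adequate for this study".

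Participation time and anticipated withdrawal makes the second operation conditional: "If the second eye receives an indication for phacoemulsification surgery, data for this second eye will also be collected". Footnote c of Table 1 repeats the condition.

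Under OPE estimation, the acoustic parameters are "correlated with the maximum energy used in the phacoemulsification surgery for each participant eye". Significance is judged with a 95% confidence interval and a multiple comparison correction. Under Cataract type and severity estimation, all participants/eyes examined with the device enter the analysis, sensitivity must exceed 90% at a 5% significance level, and several classifiers are trained: "The performance of the different classifiers will be compared". None of these sections mentions the pairing of eyes.

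**The concern.** Two eyes of one person share age, systemic exposures, examiner and usually surgeon, so they tend to resemble each other in lens properties and in the energy used. Two things follow.

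First, the adequacy statement counts each participant twice. LOCS III grades an eye, while the groups are made of people. If the two eyes differ in grade, ten people in a severity group do not supply 20 eyes of that severity.

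Second, a correlation computed over eyes with an ordinary 95% interval treats the two eyes as separate evidence. The interval is then too short, and acoustic parameters with no relation to energy are declared related too often. The phase 2 energy predictions are built on those correlation curves, so a spurious predictor carries forward. The sensitivity criterion carries the same risk if it is tested by eye.

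**Working it through.** **Reproducing the plan's figure.** Phase 1 has 40 participants in 4 equal groups: 40 / 4 = 10 participants per group, and 10 × 2 = 20 eyes per group. The stated 20 per arm is therefore the phase 1 count with both eyes of every participant included. Counting both phases would give (40 + 10) × 2 / 4 = 25, which does not match.

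**Is 20 eyes per grade assured?** The group is set by LOCS III, but the article does not say by which eye. The second eye's surgery depends on whether that eye receives an indication. A participant can therefore enter a cataract group with a fellow eye that is not referred. This shows that the count may fall short, not that it will.

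**Inputs for the inference.** The inter-eye correlation is not in the document. I assume 0.3, 0.5 and 0.8.

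**Energy correlations.** Let ρx and ρy be the inter-eye correlations of an acoustic parameter and of maximum energy. With both eyes operated and no true association, the variance of the eye-level correlation is inflated by 1 + ρx·ρy. The standard error is too small by the square root of this, and a nominal 5% two-sided test has error 2 × [1 − Φ(1.96 / factor)].

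| ρx = ρy | 1 + ρxρy | SE factor | Type I error |
|---|---|---|---|
| 0.3 | 1.09 | 1.04 | about 6% |
| 0.5 | 1.25 | 1.12 | about 8% |
| 0.8 | 1.64 | 1.28 | about 13% |

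A simulation with 30 participants (the three cataract groups), both eyes operated and no association gave 6.5%, 8.4% and 13%, in agreement.

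If only some participants contribute two eyes, replace ρxρy by f·ρxρy, where f is the share of analysed eyes that belong to a complete pair. For example, with 15 of 30 participants operated in both eyes there are 45 eyes, 30 of them paired, so f = 30/45 = 0.67. At 0.5 the inflation is 1 + 0.67 × 0.25 = 1.17, the SE factor 1.08 and the error about 7%.

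**Per-eye proportions (such as sensitivity).** For complete pairs the design effect is 1 + ρ, where ρ is the inter-eye correlation of the outcome:

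- ρ = 0.3: 20 / 1.3 = 15.4 independent eyes
- ρ = 0.5: 20 / 1.5 = 13.3
- ρ = 0.8: 20 / 1.8 = 11.1

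At ρ = 0 the 20 eyes count in full; at ρ = 1 they count as 10.

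**The case against.** The strongest reply is that this is a condensed article on a pilot. Clustered variances and cross-validation details commonly sit in a full protocol or analysis plan that is not shown. The article never calls eyes independent, it disclaims any sample size estimate, and it describes the performance evaluation as preliminary.

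Much of that stands. Independence is inferred from the eye count and the per-eye correlation, not stated. But the eye-based adequacy statement and the unspecified basis for a participant's group are in the article itself, and an analysis plan would not repair them. The OPE section is not silent about inference either: it names the unit, the interval and the correction, and as written these omit pairing. Pilot status does not remove the issue, because the Feasibility assessment section sets pass/fail criteria, one of them with a significance level.

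A reader might infer three stronger points that the document does not support:

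- **That the stated sensitivity intervals are too narrow.** No interval for sensitivity is specified. The loss of information applies only if the 5% level test is done by eye.
- **That classifier performance is inflated by leakage between fellow eyes.** No resampling scheme is given, so this is only a possibility. It could affect only the phase 1 choice of classifier, since phase 2 uses a new dataset from further participants.
- **That the proportion design effect 1 + ρ applies to the energy correlations.** It does not; the inflation there is 1 + ρxρy, which is milder.

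**Conclusion.** The point holds in a limited form. It is certain that 20 per arm is both eyes of 10 participants, that the rule for setting a participant's group is not stated, and that 20 eyes per grade is not assured. The OPE correlations, if analysed as written, are anti-conservative whenever eyes of one person are positively correlated in both variables. The effect is small at an inter-eye correlation of 0.3 and material at 0.8, as the table above shows. These sizes rest on an assumed correlation, taken as equal in both variables, and on both eyes being operated. With fewer complete pairs the effect shrinks, and with zero correlation in either variable it vanishes. The mismatch between grouping people and counting eyes remains in every case.

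**What to change.** - Restate the size as 10 participants (up to 20 eyes) per group in phase 1.
- Label every eye by its own LOCS III grade for training and evaluation, and state how the participant's group is set (for example, by the worse eye).
- For the energy correlations, use a mixed model with a participant random effect, or participant-clustered intervals (GEE or a bootstrap that resamples participants). Do the same for any per-eye test of sensitivity.
- Where resampling is used in phase 1 to compare classifiers, keep both eyes of a participant on the same side of each split.

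The cost is a few sentences of wording and standard software, with no additional participants. Intervals will be somewhat wider. With about 10 participants in a group, clustered standard errors are themselves imprecise, so a small-sample correction is sensible.
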